### Intervention

The intervention consists of eight home-based sessions of sitting Tai Chi. Tai Chi is a traditional Chinese exercise that combines rhythmic and flowing patterns of bodily movements with coordinated breathing and mindful meditation [30]. It is a moderate-intensity aerobic exercise at about 3 to 6 metabolic equivalents [31]. It has been successfully implemented in the local older population [32] and, as a low impact exercise, it is associated with a lower risk of musculoskeletal injury making it a suitable form of exercise for older adults. Since the current study includes persons with significant cognitive impairment, we adopt sitting Tai Chi which is a simpler version of Tai Chi developed by Hong Kong Polytechnic University [33]. The exercise consists of 12 steps, which include weight shifting in different sitting positions, trunk and upper limb movements, and alternate thigh lift in a smooth and coordinated manner [33].

Four weekly exercise sessions will be arranged over the first 4 weeks, and four more biweekly sessions over the next 8 weeks. Each session will last for 1 h, which starts with 10 min of warm-up activities followed by 40 min of sitting Tai Chi practice and, lastly, 10 min of cool-down exercises. The caregiver-care-recipient dyads will practise Tai Chi in their home under the instruction of a Tai Chi teacher with more than 20 years of teaching experience, and a trained research assistant. In order to monitor the progress and address participants’ concerns, biweekly phone contacts will be made during the study period (12 scheduled phone contacts in 24 weeks). On completion of the eight home-based Tai Chi sessions, participants will be given a manual and training video with detailed instructions of the Tai Chi poses to facilitate their continuation of Tai Chi practices.

A standard nonexercise social contact will be provided to the participants in the control group. Since social contact may be beneficial to one’s mood and may contribute to any improvement observed in the intervention group, we provide participants in the control group with a level of social contact equivalent to the intervention group. They will be visited by the research assistant eight times over 12 weeks. The visits involve a series of conversations related to neutral topics that are designed according to the principles of a befriending programme [34]. These topics are structured and standardised, and do not involve any topic concerning physical activity. Similar to the intervention group, 12 biweekly phone calls will be made during the study period to offer a comparable level of social contact.

### Primary outcome

Participants will be assessed at baseline, 6th week, 12th week and 24th week for their responses to intervention. The assessment schedules for caregivers and care recipients are described in Table 1. The primary outcome of the study is the proportion of participants who are classified as responders by the Hamilton Rating Scale for Depression (HAM-D-17) [35]. HAM-D-17 is a widely used and reliable measure of depressive symptoms. The scores range from 0 to 52, with higher scores indicating greater depression severity. Response to the intervention is defined as a reduction of the HAM-D-17 total score by ≥50 % from baseline to endpoint. Assessors will follow the structured interview guide for the Hamilton Depression Rating Scale (SIGH-D) when administering the HAM-D-17 [36].

**Table 1 Tab1:** Assessment schedule for caregivers and care recipients

	Baseline assessment	Week 6	Week 12	Week 24
Caregiver only				
GDS (screening only)	√			
HAM-D-17	√	√	√	√
ZBI	√	√	√	√
SF-12	√		√	√
EXIT25	√		√	√
IPIP	√			
Care recipients only				
CSDD	√	√	√	√
NPI	√		√	√
DAD	√		√	√
MBI	√		√	√
Caregivers and care recipients				
MMSE	√		√	√
Digit span	√		√	√
Delayed recall	√		√	√
CVFT	√		√	√
BBS	√		√	√
FR	√		√	√
TUG	√		√	√
Logbook	√	√	√	√
Pedometer	√	√	√	√
*BDNF* genotype	√			
Body weight and height	√		√	√
Blood pressure and pulse	√		√	√

*BBS* Berg Balance Scale, *BDNF* brain-derived neurotrophic factor, *CSDD* Cornell Scale for Depression in Dementia, *CVFT* Category Verbal Fluency Test, *DAD* Disability Assessment for Dementia, *EXIT25* Executive Interview, *FR* Functional Reach, *GDS* Geriatric Depression Scale, *HAM-D-17* Hamilton Rating Scale for Depression, *IPIP* International Personality Item Pool, *MBI* Modified Barthel Index, *MMSE* Mini Mental State Examination, *NPI* Neuropsychiatric Inventory, *TUG* Timed Up and Go, *ZBI* Zarit Burden Interview

Assessment for caregivers only:The Zarit Burden Interview (ZBI) [37] is a 22-item self-administrated questionnaire specially designed to measure the stresses experienced by caregivers of persons with dementia. Caregivers will assess the impact of the patient’s disabilities on their lifeThe SF-12 Health Survey (SF-12) [38] measures the health-related quality of life and gives two component scores: a physical component summary (PCS) and a mental component summary (MCS)The Executive Interview (EXIT25) [39] is a 25-item screening instrument developed to assess executive cognitive dysfunctionThe International Personality Item Pool (IPIP) [40] consists of 50 items assessing the ‘Big Five’ personality traits: openness to experience, conscientiousness, extraversion, agreeableness, and neuroticism

Assessment for care recipients only:The Cornell Scale for Depression in Dementia (CSDD) [41] is a clinician-rated instrument measuring depressive symptoms in persons with cognitive impairmentThe Neuropsychiatric Inventory (NPI) [42] assesses the frequency and severity of neuropsychiatric symptoms across 12 domains including psychotic features, mood changes, activities disturbances and vegetative symptomsThe Disability Assessment for Dementia (DAD) [43] evaluates functional abilities in both basic and instrumental activities of daily living in people with dementiaThe Modified Barthel Index (MBI) [44] measures individuals’ performance on 10 activities of daily living: eating, personal hygiene, bathing, toileting, dressing, bowel control, bladder control, transfers, walking, and stair climbing

Assessment for both caregivers and care recipients:Sociodemographic information includes age, gender, education level and marital statusLifestyle factors such as smoking, drinking, and sleeping habits. Health-related information like chronic health problems and medications will also be recorded. Resting blood pressure and heart rate will be taken. Body height and weight will also be measured to calculate Body Mass IndexGlobal cognitive function will be measured by the MMSE [29], digit span, delayed recall, and the Category Verbal Fluency Test (CVFT) [45]Balance ability and functional mobility will be measured by the Berg Balance Scale (BBS) [46], the Functional Reach (FR) test [47], and the Timed Up and Go (TUG) test [48]Physical activity and programme adherence will be assessed using logbook recordings. Before each assessment, participants will be asked to wear a pedometer for 1 week. Number of walking steps, history of falls, frequency, duration, and type of exercises during the week will be recorded in the logbookPhysiological markers – to examine the role of the *BDNF* Val66Met polymorphism in the antidepressant effect of exercise, buccal swabs will be collected at the baseline assessment

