**Methods/design:**

This is a parallel-group, assessor-blind, randomised controlled trial. A total of 136 caregiver-care-recipient dyads (i.e. 272 participants in total) will be recruited and randomly allocated to either a home-based structured exercise (sitting Tai Chi) group or a social contact control group. The trial comprises a 3-month intervention phase followed by an extended observation phase of another 3 months. All participants will be assessed at baseline, 6th week, 12th week and 24th week. The primary outcome will be the reduction in depression among caregivers as measured by the Hamilton Rating Scale for Depression. The secondary outcomes will be burden, quality of life, cognitive performance and balance ability of the caregivers, as well as the neuropsychiatric symptoms, cognitive function, balance and functional abilities of the persons with dementia. We will also examine whether the brain-derived neurotrophic factor gene modulates mood changes in response to exercise.

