### Sample size calculation

The sample size is calculated by the proportion of caregivers who respond to the intervention as indicated by the HAM-D-17. Taking reference of the previous study [49], we expect a 30 % reduction in the proportion of participants rated as depressed in the control group with social contact only. Assuming that a further 30 % reduction is achieved by sitting Tai Chi, we need 56 caregiver-care-recipient dyads (i.e. 112 participants) in each arm to identify a significant effect at a two-tailed alpha of 0.05 and 80 % power. Allowing for 20 % dropout, the number of dyads in each arm will rise to 68. A total number of participants of 272 will be recruited.

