### Statistical analyses

Baseline differences in demographic and clinical characteristics between the intervention and control groups will be evaluated by chi-square and independent sample *t* tests. All data will be analysed using the intent-to-treat principle. For outcome measures that are not normally distributed (e.g. the HAM-D-17), log transformation will be applied to perform the analyses. Mixed-effects models will be fitted for each outcome measure using baseline, 6th, 12th and 24th week follow-up data. Possible confounding factors such as sex, age, and use of antidepressant medication will be treated as time-dependent covariate in the mixed-effects models. If applicable, subgroup analysis will be carried out to estimate whether there is any gender difference (female versus male caregivers) regarding the effect of the intervention in alleviating depressive symptoms. Fixed effects for time, intervention group, and their interactions will be examined and unstructured covariance structure will be employed to account for the within-subject correlation over time. Levels of significance will be set at *p* < 0.05. All analyses will be performed using SPSS version 20.0 (SPSS Inc., Chicago, IL, USA).

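### The trial is defined and sized on a responder proportion, but the mixed-effects analysis described does not fit that outcome and no comparison of proportions is given

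*Protocol article*

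**What the plan says.** Four places in the protocol article bear on this.

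- **Primary outcome:** "The primary outcome of the study is the proportion of participants who are classified as responders" on the HAM-D-17. The criterion follows: "Response to the intervention is defined as a reduction of the HAM-D-17 total score by" 50% or more, between baseline and an endpoint to which no visit is attached.
- **Sample size calculation:** "The sample size is calculated by the proportion of caregivers who respond to the intervention as indicated by the HAM-D-17".
- **Statistical analyses:** "For outcome measures that are not normally distributed (e.g. the HAM-D-17), log transformation will be applied to perform the analyses". Then: "Mixed-effects models will be fitted for each outcome measure using baseline, 6th, 12th and 24th week follow-up data". The model terms are also given: "Fixed effects for time, intervention group, and their interactions will be examined and unstructured covariance structure will be employed". The only test suited to proportions is the chi-square, and it is reserved for baseline characteristics, which "will be evaluated by chi-square and independent sample" t tests.
- **Abstract, Methods/design:** "The primary outcome will be the reduction in depression among caregivers as measured by the Hamilton Rating Scale for Depression", with no responder criterion.

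**The concern.** The outcome and sample size sections agree on a binary outcome. The analysis section handles the HAM-D-17 as a transformed score followed over time. These are different hypotheses: one concerns the difference between arms in the proportion who respond, the other the difference between arms in the course of the log score.

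Two things are at stake. The test that the sample size supports is not the one the analysis section describes, and the test it does describe has no stated power. And because response is called primary while the score is what gets modelled, the choice of headline result could be made after both are known. The nominal 5% error rate then no longer attaches to one pre-specified test.

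**Working it through.** **1. Which quantity the sample size supports.** Inputs from the Sample size calculation section: 30% improvement in controls, a further 30% with Tai Chi (read as absolute, 0.30 v 0.60), two-sided alpha 0.05, power 80%, 56 dyads per arm.

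Pooled two-proportion formula, with mean proportion 0.45:

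n = [1.960 × √(2 × 0.45 × 0.55) + z × √(0.30 × 0.70 + 0.60 × 0.40)]² / 0.30²

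- 80% power (z = 0.842): [1.379 + 0.565]² / 0.09 = 41.97, so 42 per arm (49 with continuity correction).
- 90% power (z = 1.282): [1.379 + 0.860]² / 0.09 = 55.68, so 56 per arm. Power at 56 per arm is 90.2%.

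The stated 56 is therefore not reproduced at the stated 80% on this reading, although it matches 90%. If the further 30% is relative (0.70 v 0.49 still depressed), 85 per arm are needed. That discrepancy is a separate matter. What counts here is that the inputs are proportions: no standard deviation or mean difference for the HAM-D-17, raw or log, is given anywhere.

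**2. Whether the described model can produce the primary comparison.**

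| Feature of the described model | HAM-D-17 score | Responder status |
|---|---|---|
| Value at baseline | Yes | No: defined as change from baseline |
| Log transformation | Possible | Not meaningful for yes/no |
| Visits in the model | Baseline, weeks 6, 12, 24 | At most weeks 6, 12, 24; one only if a single endpoint is meant |
| Contrast named as primary | None | None |

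The score fits the described analysis. Responder status does not.

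**3. Power of what is described.** It cannot be derived from the document. As a rough guide only, a single-visit comparison of means with 56 evaluable per arm detects (1.960 + 0.842) × √(2/56) = 0.53 standard deviations with 80% power. Without a standard deviation or expected difference, that cannot be set against any planned effect.

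**4. Cost of leaving both results available as primary.** Take one visit, no true effect, and two tests (responder and score), each at two-sided 0.05, with bivariate normal test statistics. The correlation between them is an assumption. The probability that at least one is significant is 1 − P(|Z₁| < 1.96 and |Z₂| < 1.96):

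- correlation 0.6: 8.8%
- correlation 0.7: 8.3%
- correlation 0.8: 7.8%

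Independent tests would give 1 − 0.95² = 9.75%.

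**The case against.** The strongest reply is that this is a condensed article, and that a named test for the primary outcome is commonly left to the analysis plan. The text never says that the mixed models are linear or assume normality. That is an inference from the log transformation and the unstructured covariance. A mixed model for each outcome could include a binary one, and response could be derived at each of weeks 6, 12 and 24. This stands in part: a reader might infer that the plan commits to a linear model and so never tests response at all, and the wording does not go that far. But the section is not silent. It prescribes baseline data for every outcome and a log transformation for the HAM-D-17, and neither can apply to a status defined as change from baseline. An analysis plan that compared responder proportions would have to depart from what the article states.

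A reader might also infer two rival primary outcomes from the abstract. The document does not clearly support that. The abstract speaks of reduced depression as measured by the scale, not of a mean or a change score, and this may be shorthand for response. It adds ambiguity, but the conflict between the outcome and analysis sections exists without it.

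Finally, a reader might count visits as well as outcomes. Under assumed correlations of 0.6 between weeks and 0.6-0.8 between outcomes, this gives 13-15% over weeks 12 and 24, and 18-20% with week 6 added. Those figures mix in the undefined endpoint visit, a distinct defect, and should not be charged to this one.

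**Conclusion.** Wrong as written. The primary outcome and the sample size rest on a responder proportion. The analysis described for the HAM-D-17 tests the log score with no stated power, and the powered comparison is not described. This conclusion follows from setting the sections side by side and depends on no numerical assumption.

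The size of the error-rate problem is conditional. It is about 8-9% instead of 5% if either the responder or the score result at a single visit could be presented as primary, given a correlation of 0.6-0.8 between the tests, which the document does not supply. Nothing in the article shows that such selection is intended; the plan simply does not exclude it.

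**What to change.** Keep response as the primary outcome, since the trial was sized on it, and name a single endpoint visit for it. In Statistical analyses, replace the mixed model for this outcome with a logistic regression of response on group, with baseline HAM-D-17 as covariate, in all randomised caregivers and with missing scores multiply imputed. State that the mixed model of the HAM-D-17 score is secondary. Reword the abstract so that it gives the same responder criterion as the Primary outcome section.

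Making the score primary instead would also be coherent, but it drops the outcome on which the trial was sized, and the document gives no standard deviation from which to show that 56 evaluable per arm is enough.

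The cost is a small amount of extra analysis and wording, with no new data and no additional participants. The article reports that recruitment was still open at submission; the change should be made before unblinding.

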### Sample size calculation

The sample size is calculated by the proportion of caregivers who respond to the intervention as indicated by the HAM-D-17. Taking reference of the previous study [49], we expect a 30 % reduction in the proportion of participants rated as depressed in the control group with social contact only. Assuming that a further 30 % reduction is achieved by sitting Tai Chi, we need 56 caregiver-care-recipient dyads (i.e. 112 participants) in each arm to identify a significant effect at a two-tailed alpha of 0.05 and 80 % power. Allowing for 20 % dropout, the number of dyads in each arm will rise to 68. A total number of participants of 272 will be recruited.

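### The 56 dyads per arm for 80% power cannot be reproduced from the stated inputs: one reading needs 42 per arm, the other 85

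*Protocol article*

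**What the plan says.** All the inputs are in the section Sample size calculation of the protocol article.

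- Quantity used for sizing: "The sample size is calculated by the proportion of caregivers who respond to the intervention as indicated by the HAM-D-17".
- Control arm: "we expect a 30 % reduction in the proportion of participants rated as depressed in the control group with social contact only", with reference to a previous study.
- Tai Chi arm: "Assuming that a further 30 % reduction is achieved by sitting Tai Chi".
- Error rates and result: "we need 56 caregiver-care-recipient dyads (i.e. 112 participants) in each arm to identify a significant effect at a two-tailed alpha of 0.05", with 80% power.
- Dropout: a 20% allowance, after which "the number of dyads in each arm will rise to 68", making 272 participants (136 dyads).

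The section Primary outcome gives the definition that the sizing should rest on: "Response to the intervention is defined as a reduction of the HAM-D-17 total score by ≥50 % from baseline to endpoint".

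The sample size section does not say whether the further 30% is absolute or relative. It names no test or formula, and gives no baseline proportion of caregivers rated as depressed.

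**The concern.** A sample size paragraph that prints its rates, alpha, power, number per arm and dropout should be reproducible from them. This one is not, and the gap runs in opposite directions depending on how one phrase is read. On the absolute reading the trial is larger than 80% power requires; on the relative reading it is well short. Someone interpreting a null result could not tell whether the trial had about 90% or about 60% power for the effect that the sponsor had in mind.

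The paragraph also moves between two quantities. It opens with response, which elsewhere means a fall of at least half in the HAM-D-17 total. It then takes its rates from the proportion rated as depressed, which is a status at one time. A caregiver can halve the score without changing status, or change status without halving the score. The assumed rates are therefore not stated for the primary endpoint.

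**Working it through.** **Inputs.** Two-sided alpha 0.05 (z = 1.960), power 80% (z = 0.842), equal arms, stated n = 56 per arm, dropout 20%, 68 per arm after inflation. All come from Sample size calculation. The two proportions have to be inferred, so each reading is worked separately.

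**Formula** (pooled two-proportion, no continuity correction), with d the difference and p̄ the mean of the two proportions:

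n = [1.960·√(2p̄(1−p̄)) + z_power·√(p1(1−p1) + p2(1−p2))]² / d²

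**Reading A: absolute, taken as response of 30% v 60%.** Here p̄ = 0.45, 2p̄(1−p̄) = 0.495, the sum of variances is 0.21 + 0.24 = 0.45, and d = 0.30.

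- 80% power: [1.960×0.7036 + 0.842×0.6708]² / 0.09 = 41.97, so **42** per arm.
- 90% power (z = 1.282): 55.68, so **56** per arm.
- Power at 56 per arm: Φ[(0.30×√56 − 1.960×0.7036) / 0.6708] = Φ(1.291) = **90.2%**.

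The choice of method does not bring 80% power up to 56:

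| Method, 30% v 60%, 80% power | n per arm |
|---|---|
| Pooled | 42 |
| Unpooled | 40 |
| Pooled variance in both terms | 44 |
| Arcsine | 42 |
| Continuity-corrected | 49 |
| Fisher exact | about 48 |
| One-sided, without / with continuity correction | 33 / 40 |

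Fisher exact power at 56 per arm is 85.7%. With continuity correction, 90% power needs 63.

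**Reading B: relative, 70% v 49% still depressed** (0.70×0.70 = 0.49). Here p̄ = 0.595, 2p̄(1−p̄) = 0.48195, the sum of variances is 0.21 + 0.2499 = 0.4599, and d = 0.21.

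- 80% power: [1.960×0.6942 + 0.842×0.6782]² / 0.0441 = 84.6, so **85** per arm (94 with continuity correction).
- Power at 56 per arm: Φ[(0.21×√56 − 1.960×0.6942) / 0.6782] = Φ(0.311) = **62.2%** (Fisher exact 54.4%).

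**Reading C: both reductions as fractions of an unstated baseline proportion depressed, π.** The arms are then 0.7π and 0.4π. The document gives no π, so these values are assumptions:

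| π | n per arm for 80% | Power at 56 |
|---|---|---|
| 1.0 | 42 | 90% |
| 0.9 | 53 | 82% |
| 0.88 | 56 | 81% |
| 0.8 | 66 | 73% |
| 0.7 | 84 | 63% |
| 0.6 | 106 | 53% |

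At π = 0.88 the arms are 61.6% v 35.2% and the formula gives 55.06, so 56. If the reductions are instead percentage points taken off π, the largest requirement is for 65% v 35%: [1.960×√0.5 + 0.842×√0.455]² / 0.09 = 42.4, so 43.

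**Dropout.**

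- 56×1.2 = 67.2, which rounds up to 68, so 68 is consistent with multiplying by 1.2.
- 68×0.8 = 54.4 remain, fewer than 56.
- To keep 56 after 20% loss: 56/0.8 = 70.
- Loss that 68 can absorb: 1 − 56/68 = 17.6%.
- Power with 54 per arm: 89.1% (reading A) or 60.6% (reading B).

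**The case against.** **An input may have been left out.** A reduction in a proportion implies a starting proportion, and the rates come from a cited study that is not shown. With a baseline of about 0.88 the stated 56 at 80% power is right. This stands as a limit on the conclusion: what can be shown is that the figure does not follow from the printed inputs, not that 80% is false. It does not rescue the paragraph, because 0.88 appears nowhere. Nor can a high baseline be presumed: the inclusion criteria admit only caregivers below the local GDS cut-off for clinically significant depression. At an assumed baseline of 0.6, power at 56 would be 53%.

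**A reader might infer that the trial was planned at 90% power and mislabelled.** The match is exact for the uncorrected pooled formula and holds for the arcsine formula, but continuity correction needs 63 and Fisher's test at 56 gives about 86%. With no test named, the document cannot confirm this.

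**A reader might infer that the trial is underpowered.** That follows only on the relative reading or with a baseline below about 0.87. On the most natural reading the discrepancy is conservative: 54 completers exceed the 42 needed.

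**Equating 30% v 60% response with 70% v 40% still depressed is itself an assumption.** This is correct, since the two quantities differ. Reading A is therefore conditional on the rates being meant for response.

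**The dropout error is small.** It is two dyads per arm and about one percentage point of power. The section Statistical analyses also plans intent-to-treat and mixed models using all visits, to which early leavers may still contribute. It is a side note.

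**Conclusion.** The stated 56 per arm at two-tailed alpha 0.05 and 80% power does not follow from the stated inputs. Read as absolute response rates of 30% v 60%, the requirement is 42 per arm (49 with continuity correction), and 56 gives about 90% power uncorrected or about 86% by Fisher's exact test. Read as relative, the requirement is 85 and 56 gives about 62%. Only an unstated baseline of about 0.88 recovers the printed figure. The dropout inflation falls two dyads per arm short of its own target and is secondary.

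These figures assume equal arms and a single comparison of two proportions. They do not show which reading the sponsor intended, and they do not show that the recruitment target is too small.

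**What to change.** Reword the sample size paragraph and leave the recruitment target at 68 dyads per arm. It should:

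1. give the two assumed response proportions on the definition in Primary outcome (a fall of at least 50% in HAM-D-17), and explain how they were derived if the source reported the proportion depressed, including any baseline proportion used;
2. say whether the difference is absolute or relative;
3. name the test and the endpoint visit, which the sponsor must supply because the protocol says only that response runs from baseline to endpoint;
4. restate the power for 68 randomised per arm with 20% dropout (about 54 evaluable).

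If 30% v 60% was meant, the text could read: *Assuming response of 30% on control and 60% on Tai Chi at [endpoint visit], an absolute difference of 30 percentage points, 68 dyads randomised per arm with 20% dropout leave about 54 evaluable per arm, giving about 89% power at two-sided alpha 0.05 (uncorrected two-proportion test).* If the relative reduction was meant, the same sentence should give 70% v 49% still depressed (30% v 51% if expressed as response) and a power of about 61%, stated openly as a shortfall.

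The cost is one reworded paragraph. Enrolment, allocation and analysis do not change.
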